## SUMMARY

### Rationale

The growing group of family caregivers of dementia patients has a highly increased risk of developing depressive and anxiety disorders. An American landmark study reported substantial beneficial effects of family meetings on depression in family caregivers as well as on delay of institutionalisation of patients. Effects are not replicated in other countries yet. When effective, family meetings can be an important addition to the current care services in the Netherlands.

### Objective

To investigate the effectiveness of family meetings on prevention of anxiety and depressive disorders (DSM IV) and symptom levels of primary family caregivers of patients with dementia. To perform an economic evaluation alongside the trial.

### Study design

Randomised controlled clinical trial comparing structured family meetings versus usual care with significant others of 172 primary family caregivers of community dwelling demented patients recruited in memory clinics with a follow up of 24 months.

### Study population

Dyads of diagnosed dementia patients and their central informal family caregiver. The unit of analysis is the caregiver.

### Intervention

Four meetings with family and close friends will be organized and run by a trained counsellor according to a manual (Mittelman 2003). The aim is to offer psycho-education, increase problem-solving skills and mobilize the naturally existing social network of patient by sharing support tasks of network members.

### Main study parameters/endpoints

Incidence of anxiety and depressive disorders (DSM IV minor, major depression, generalised anxiety, panic disorder, phobic disorders) assessed with the Mini-International Neuropsychiatric Interview (MINI). The *dimensional* or severity measure of anxiety and depression *symptoms* is derived by validated self report instruments: the Centre for Epidemiologic Studies Depression Scale (CES-D) and Geriatric Depression Scale (GDS-5) for depression and the anxiety subscale of the Hospital Anxiety and Depression scales (HADS) for anxiety. Additional questionnaires are used to explore profiles of caregivers who are best helped by the intervention.

### Nature and extent of the burden and risks associated with participation, benefit and group relatedness

The burden of the intervention will be minimal for the dementia patients and their family caregivers. A possible burden can be created by the number of questionnaires which will be taken to assess the study parameters. Furthermore, emotional discomfort and family conflicts can exist as a consequence of participation in the intervention. This possible burden will be in proportion to the potential value of the research.

## **1 INTRODUCTION AND RATIONALE**

### **1.1 Motivation**

Our hypothesis is that affective disorders (i.e. depressive or anxiety disorders) of dementia caregivers who are already at risk for such disorders are largely preventable. Systematic reviews and meta-analyses show that information and support alone is helpful but only address the psychological needs of caregivers modestly at best (Sorensen 2002, Brodaty 2003). Programs that demonstrate beneficial effects on affective disorders involved both patients and their families, are more intensive and modified to caregivers needs (Brodaty 2003, Acton 2002). As demonstrated in the landmark studies of Mittelman et al., family meetings, designed to mobilize support of naturally existing family networks, appear to be among the most powerful psychosocial interventions to reduce depression in caregivers (Whitlatch 1991, Mittelman 1995, 1996, 2004). However, these studies have not been replicated elsewhere. Family counselling can maximise the positive contributions of each member to caregiving, prevent one member from carrying the entire weight of the caregiving role, improve the caregiver's understanding of how to ask for help, what kind of help is reasonable to expect from family members, and how to accept help, and reduce family conflict. In addition, these programs resulted in postponement of nursing home placement of patients, while maintaining a comparable or better quality of life of the caregivers.

Our study has several modifications compared to the work of Mittelman. Mittelman's studies were performed among spouse caregivers of patients with Alzheimer type dementia only. The question remains whether the intervention is robust when a group of caregivers is included that is more heterogeneous. Spouses, children, neighbours, and friends may play a caring role. The effects of family meetings on child-caregivers and in carers of non-Alzheimer type dementia patients are not studied yet. Also, possible preventive effects on anxiety, a frequent co-morbid condition in depressed caregivers, were not evaluated yet. Mittelman's intervention consisted not only of family meetings but also of individual counselling and support groups for caregivers, as well as the possibility of telephone counselling for caregivers and other family members as needed. Much of the beneficial effects were attributed specifically to the family meetings. However, it remains to be seen whether family meetings alone will demonstrate comparable preventive effects.

Despite its great potential, Dutch health care professionals rarely organise family meetings. In this age of shared care, memory clinics seem especially well suited to organize family meetings: a) memory clinics are enthusiastic to participate, b) they already have the necessary expertise, the personal and/or are willing to learn; c) family meetings are a logical next step for them: their usual practice traditionally focused on the medical aspects, the diagnostics of memory problems and medication management since anti-Alzheimer medication has become available (Verhey 2005). Family meetings also have a social diagnostic dimension (assessment of support); d) The number of Dutch memory clinics has increased rapidly to about 40 currently. They already diagnose about 25% of all dementia patients (coming from 5% in 1998) and this percentage is expected to increase further to about 50% over the next years (Verhey 2005). Nevertheless, family meetings are rare and are not performed in a systematic way with follow up meetings.

### **1.2 Scientific and social relevance**

#### **Impact**

Many studies demonstrated the enormous impact of depressive and anxiety disorders and symptoms on the quality of life. Depressive disorders rank second in the World Health

Organisation's list of disorders with the most quality adjusted life years lost (Murray 1997). Anxiety disorders are strongly associated with depressive disorders and represent a comparable burden (Beekman 2000).

Family caregivers have an extremely high risk of becoming depressed or anxious as well as a higher mortality risk, and family caregivers of persons with dementia even more so than other caregivers (Schulz 1999). Dementia is strongly associated with aging: the prevalence figures double every five years of increase in age (Hofman 1991). In our rapidly aging population the projection of dementia prevalence in 2050 will have doubled (GR2002).

Despite a wide range of useful services that can help patients and relief caregivers, the burden of caregiving remains very high (Schulz 1999). Long term institutionalisation of persons with dementia is extremely costly. The mental health of the family caregiver is often decisive in the timing of nursing home placement. Any intervention that can relieve the burden of caregiving and (thereby) prevent mental health problems of caregivers is important. In addition, if such efforts can delay nursing home placement they are likely to be extremely cost-effective.

The family can be both an invaluable aid to a caregiver and a source of stress. Three quarters of dementia caregivers reported conflict with family members who were not seen as doing their share of caregiving and 73% of the dementia caregivers reported mental and physical health problems compared to 50% respectively 22% of non-dementia caregivers (AARP 1997). In general, 76% of caregivers care with satisfaction; only 13% feels obligated to do so (SCP 2003). These caregivers should be enabled to provide care without becoming a patient themselves.

### **Target group**

Family members of persons with dementia, often at great personal cost, provide much of the care for older adults with dementia in the community (Cohen 1999). Family caregivers of dementia patients have an extremely high risk developing affective disorders such as major depression and anxiety disorder, with women and spouses at even higher risk (Cuijpers 2005, Schulz 1999). This risk persists over many years of caregiving and even after caregiving ends with the death of a care recipient (Schulz 1999, Robinson-Whelen 2001). Generic preventive screening is not advocated (Cuijpers 2002). However, especially among those who already have symptoms of distress or burden, indicated prevention may be the road forward. An additional advantage of prevention of affective disorders of caregiver is that the period until institutionalisation may be prolonged while maintaining a comparable or better quality of life of the caregivers.

Family caregivers generally prefer to avoid placing their elderly relatives in residential care, and spouse caregivers are more reluctant than other relatives to do so. Family caregivers willingness to care has not declined over the last decade as might be expected due to loosening of family ties (SCP 2003, STG 1990). Professional services should at least offer as much effective evidence based outpatient support as possible.

### **Prevalence and incidence**

The month prevalence of depressive disorders among caregivers varied between 15-32% in three representative community samples, the 12 months incidence of depressive disorders was 48% as reported in one representative sample (Cuijpers 2005, Ballard 1996). Data on anxiety disorders in dementia caregivers are scarce but suggest that 1 in 3 caregivers suffers from an anxiety disorder (Akkerman 2004). Depressive and anxiety symptoms are even more prevalent and affect between half to three-quarter of all caregivers (Cuijpers 2005, Ballard 1996, AARP 1997).

The estimated prevalence rate of dementia among community dwelling elderly aged 65 to 95 is 6.6% (Hofman 1991). In the Netherlands, currently 1 in 93 persons suffer from dementia (about 200.000 patients). Two third lives at home and a family member cares for most of them. A cure for dementia is not within reach in the near future. Over the next years, the number of demented elderly will increase substantially and so will be the numbers of family caregivers caring for a demented person. In 2050, as a result of aging populations, about 1 in 44 persons will be demented (GR 2002). Consequently, the number of informal caregivers, at risk for psychological morbidity, will have doubled as well by that time.

Recent reports by national advisory bodies

Both nationally and internationally there is great concern regarding the enormous burden and costs of dementia related care (GR 2002, RIVM site). The Dutch national health council identified an urgent under capacity of residential facilities for demented persons, which cannot be solved in short notice.

### **Theory**

Psychosocial interventions such as empowering families' support system by counselling in family meetings, are based on the theory of the stress process that suggests that by improving certain moderators, social support and mastery over the caregiving task, it is possible to create buffers against the burden of caregiving on outcomes such as depression, anxiety, an disability to continue provide care outside of an institution (Pearlin 1978).

### **1.3 Innovation**

The effectiveness of using only the family counselling component of Mittelman's intervention has not been tested. Effects of family meetings were not replicated in other countries yet. In addition, the earlier study was done with spouse caregivers of Alzheimer type dementia patients only and measured effects on depression but not on anxiety. In our study we also include other family caregivers relations as well as non-alzheimer type dementias and measure both depression and anxiety.

Finally, economic evaluations of this intervention were not reported yet. When (cost)-effective, it can be an important addition to the current care services in the Netherlands. Are there similar studies underway: no similar studies are running currently.

## 2 OBJECTIVES

### 2.1 Primary Objective

To investigate the effectiveness of family meetings on the subsequent two year prevention of development of anxiety and depressive disorders (DSM IV) and symptom levels of primary family caregivers of patients with dementia.

### 2.2 Secondary Objective

An economic evaluation will be performed alongside the study to estimate the cost-effectiveness.

## 3 STUDY DESIGN

### 3.1 Design

Randomised controlled indicated prevention trial.

After selection and baseline assessment, study subjects are randomised to one of two groups; the intervention group receives usual care plus family meetings, the control group receives usual care only. Participants are free to seek additional assistance and support elsewhere at any time throughout 24 months follow-up. The study subjects are recruited through several memory clinics and specialized mental health care institutions.

### 3.2 Duration and Planning

Total 62 months: 10 months preparation; 22 months inclusion and baseline measurements, 24 months follow up, 6 months analyses and reports.

#### Planning

|                       |                                                                |
|-----------------------|----------------------------------------------------------------|
| Jan 2007 - Nov 2007   | Preparation: 10 months                                         |
| Nov 2007 - Sept 2009  | Inclusion and baseline measurement: 22 months                  |
| Sept 2009 - Sept 2011 | Follow-up: 24 months (measurements at 6, 12, 18 and 24 months) |
| Sept 2011 – Dec 2012  | Analysis and reports: 6 months                                 |

#### Time schedule

| Time schedule |             |      |       |       |     |      |      |     |           |     |           |     |
|---------------|-------------|------|-------|-------|-----|------|------|-----|-----------|-----|-----------|-----|
|               |             |      |       |       |     |      |      |     |           |     |           |     |
|               | jan         | febr | march | april | may | june | july | aug | sept      | oct | nov       | dec |
| 2007          | preparation |      |       |       |     |      |      |     |           |     | inclusion |     |
| 2008          | inclusion   |      |       |       |     |      |      |     |           |     |           |     |
| 2009          | inclusion   |      |       |       |     |      |      |     | follow up |     |           |     |
| 2010          | follow up   |      |       |       |     |      |      |     |           |     |           |     |
| 2011          | follow up   |      |       |       |     |      |      |     | analyses  |     |           |     |
| 2012          | Analyses    |      |       |       |     |      |      |     |           |     |           |     |

### 3.3 Setting

Several memory clinics and specialized mental health care institutions.

The flow chart gives an overview of the procedures that subjects will undergo in the course of research.

[figure not shown]

## **4 STUDY POPULATION**

### **4.1 Population (base)**

Caregivers and patients will be drawn from memory clinics and several memory clinics and specialized mental health care institutions with a combined annual turnover of more than 750 diagnosed dementia patients. Therefore, even bearing Lasagna's law (researchers and clinicians invariably overestimate the number of patients available for study participation) in mind, we feel confident that we can achieve our targeted number of caregiver-patients dyads within 22 months. From our previous studies, we learned that an inclusion period of 18 months is sufficient to include the required number of pairs.

### **4.2 Inclusion criteria**

- Family caregiver who takes primary responsibility for the informal care of a community dwelling patient with a clinical diagnosis of dementia.
- Both caregiver and patient have sufficient language proficiency in Dutch for adequate participation in meetings, interviews and tests.
- Written informed consent from both patient and caregiver is obtained. In case of mental incompetence of a patient the family caregiver will sign the consent for the patient.

### **4.3 Exclusion criteria**

- Severe somatic or psychiatric co-morbidity of either caregiver or patient, which will significantly impair cooperation to the program.
- Either caregiver or patient participates in other intervention studies at inclusion or during the study.
- Caregivers having a depressive or anxiety disorder.
- Scheduled to move a patient to a nursing home.

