### **4.4 Sample size calculation**

Sample size calculations are based on the expected effects of the intervention on the main outcome measures, incidence of affective disorders and increasing time to incident problems. Incidence estimates are derived from the literature and other studies performed by our group (Prevention of anxiety and depression in late life). Effect estimates are based on the primary studies of Mittelman (1996, 2004). We estimate the yearly incidence of affective disorders among caregiver at risk conservatively at 30% (Cuijpers 2005). We aim to reduce the incidence to 10% of new cases a year. With an alpha of 0.05, power of 80%, 73 persons per group are then needed. Assuming 15% loss to follow up we need to recruit  $2 \times 73 \times 100 / 85 = 172$  pairs of dementia patients and family caregivers (Statpower software). This number will be sufficient as well to measure a moderately strong reduction (Cohen's  $D > 0.5$ ) in number of depressive or anxiety symptoms.

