## **6.3 Study procedures**

After informed consent both patient and primary caregiver have to fill in several questionnaires (patients will be interviewed depending on their capabilities). The measurements at baseline and follow up (at 6, 12, 18 and 24 months after baseline) are done by independent and blinded assessors.

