## **6.4 Randomisation, blinding and treatment allocation**

Pairs are randomized after baseline measurement. We will be able to detect and monitor selection bias as eligibility of caregivers will be routinely tested during the diagnostic work up. Baseline and follow up data are gathered by independent and blinded interviewers. After randomisation, participants included in the intervention will follow the different stages (described in paragraph 5.2)

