## **6.6 Withdrawal of individual subjects**

Subjects can leave the study at any time for any reason if they wish to do so without any consequences. The investigator can decide to withdraw a subject from the study for urgent medical reasons.

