### **Follow-up of subjects withdrawn from treatment**

Data will be primarily analysed according to the Intention to treat principle, i.e. including all participants with valid data, regardless of whether they did or did not receive the intervention. Subsequently, the results of the intention to treat analysis will be compared with the results of the 'on treatment' analysis, to assess whether protocol violations have caused bias. Participants with documented deviations from the protocol (i.e. participants who did not receive the entire intervention or participants in either the intervention or the control group with incomplete

follow-up data) will be excluded from the on treatment analysis. Comparability between the intervention and usual care groups will be assessed at baseline to check differences.

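### Section 4.3 makes joining another intervention study after randomisation an exclusion criterion, and the protocol does not say that such pairs stay in follow-up and in the intention-to-treat analysis

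*Protocol*

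**What the plan says.** - **Eligibility (Protocol 4.3).** One exclusion criterion reads "Either caregiver or patient participates in other intervention studies at inclusion or during the study". It applies to either member of the pair and has no end date short of the study itself.
- **Timing (6.4 and 6.3).** "Pairs are randomized after baseline measurement". Assessments follow at 6, 12, 18 and 24 months.
- **Withdrawal (6.6).** Subjects may leave by their own choice. Beyond that, "The investigator can decide to withdraw a subject from the study for urgent medical reasons". Joining another study is not mentioned.
- **Analysis sets (6.6, follow-up of subjects withdrawn from treatment).** The primary analysis is by intention to treat, described as "including all participants with valid data, regardless of whether they did or did not receive the intervention". The secondary on-treatment analysis drops "participants who did not receive the entire intervention or participants in either the intervention or the control group with incomplete" follow-up data. Participation in another study is not on that list.
- **Other help (3.1).** "Participants are free to seek additional assistance and support elsewhere at any time throughout 24 months follow-up".

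The protocol does not say what happens to a pair that joins another intervention study at, say, month 9.

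**The concern.** An eligibility criterion can act only on what is known when a pair enters. Apart from the interval between inclusion and randomisation, the later part of this one describes behaviour after allocation. Site staff or analysts who apply it as written would find that a randomised pair has become ineligible. The protocol leaves them several options: stop follow-up, drop the pair from the analysis, censor it on joining, or keep it.

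The choice matters because joining another programme may be related to allocation and to outcome. Control caregivers receive usual care only, and the protocol describes blinding for the assessors, not for the participants. A caregiver whose distress is rising may have more reason to look for another programme, and distress is close to what the primary endpoint measures. Dropping pairs for such an event would make the Cox comparison in 6.5 depend on a selection made after randomisation. If the rule is left open, it could also be settled after outcomes are known.

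**Working it through.** **1. Setting the sections side by side**

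| Section | What it governs | Pair joins another study after randomisation |
|---|---|---|
| 4.3 | Eligibility | Excluded, if read literally |
| 6.6, withdrawal | Leaving the study | Not a listed ground for the investigator |
| 6.6, intention to treat | Primary analysis | Kept if its data are valid; not addressed by name |
| 6.6, on treatment | Secondary analysis | Not a listed reason for exclusion |
| 3.1 | Use of other help | Concerns support, not enrolment in research |

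Only 4.3 points to exclusion. The sections in 6.6 point the other way without addressing the case. The conflict with intention to treat therefore depends on 4.3 being enforced after randomisation.

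**2. The plan's own figure (4.4)**

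Inputs: 30% and 10% a year, alpha 0.05, power 80%, 73 per group, 15% loss to follow-up. I assume a two-sided test, because sidedness is not stated.

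- Uncorrected: n = [1.96·√(2·0.2·0.8) + 0.8416·√(0.3·0.7 + 0.1·0.9)]² / 0.2² = (1.109 + 0.461)² / 0.04 ≈ 61.6, so 62 per group.
- With continuity correction: (61.6/4)·[1 + √(1 + 4/(61.6·0.2))]² ≈ 71.3, so 72 per group, against 73 stated.
- Recruitment: 146/0.85 = 171.8, so 172 pairs, as stated.

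The sample size reproduces closely and does not depend on this point.

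**3. Power if pairs were removed on top of the 15% loss**

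The removal rates are assumed; the documents give none. Pairs left per group = 172·0.85·(1 − r)/2. Recruitment needed to keep 146 evaluable pairs = 146/[0.85·(1 − r)].

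| Removed, r | Left per group | Power, continuity-corrected | Pairs to recruit |
|---|---|---|---|
| 0% | 73.1 | 81.2% | 172 |
| 2% | 71.6 | 80.3% | 176 |
| 5% | 69.4 | 78.8% | 181 |
| 10% | 65.8 | 76.2% | 191 |

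**4. Possible shift in the comparison**

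The planned yearly rates give 24-month risks of 1 − 0.7² = 51% (control) and 1 − 0.9² = 19% (intervention), a difference of 32 points. Take 172/2 = 86 pairs per arm and, for simplicity, ignore other losses. Assume that k pairs join another study and have twice their arm's average hazard. Their 24-month risk is then 1 − 0.49² = 76% in the control arm or 1 − 0.81² = 34% in the intervention arm.

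For k = 9 (about 10%):

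- Control arm: (86·0.51 − 9·0.76)/77 = (43.9 − 6.8)/77 = 48.1%.
- Intervention arm: (86·0.19 − 9·0.344)/77 = (16.3 − 3.1)/77 = 17.2%.

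| k removed from an arm | Control risk left | Intervention risk left | Difference, control only affected | Difference, intervention only affected | Difference, both affected |
|---|---|---|---|---|---|
| 2 | 50.4% | 18.6% | 31.4 | 32.4 | 31.8 |
| 4 | 49.8% | 18.2% | 30.8 | 32.8 | 31.5 |
| 9 | 48.1% | 17.2% | 29.1 | 33.8 | 30.9 |

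Differences are in percentage points, against 32 planned. If the pairs that join have average risk for their arm, removing them does not shift the expected risk at all.

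**The case against.** The strongest reply is that the protocol removes nobody. Section 6.6 puts intention to treat first, and even the on-treatment exclusions do not name participation in another study. The investigator's stated ground for withdrawal is urgent medical reasons. On this view the phrase in 4.3 is a condition checked at entry: the pair should not be in another trial, nor planning to join one. The neighbouring criterion about a planned nursing-home move likewise screens at entry for a future event. A pair that joins another study and still gives data would simply stay in the primary analysis.

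Much of this stands. A reader might infer that the plan removes randomised pairs and so breaks its own primary analysis. The documents do not support that, because no section orders removal. What the reply does not do is settle the case. The criterion is worded as participation during the study, not as an intention at entry, and 6.6 does not say that such a pair is kept.

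A reader might also infer that 4.3 contradicts the freedom in 3.1 to look for other help. It does not. Section 3.1 concerns assistance and support, while 4.3 concerns enrolment in intervention studies. A caregiver can use respite care or home nursing without joining a trial, and 6.1 lists formal care support among the potential confounders and modifiers. The two meet only where the support is itself delivered within a study.

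Nor does the restriction to valid data in 6.6 show that these pairs are lost, since joining another study does not make an outcome measurement invalid. The wording only fails to say expressly that all randomised pairs are kept.

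Finally, the bias mechanism is plausible but not documented. The criterion can also be triggered by the patient's enrolment, which need not follow the caregiver's distress or the arm.

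**Conclusion.** The point holds as a defect of wording with a possible analytic consequence. Section 4.3 contains an exclusion that mostly cannot be applied before randomisation, and the protocol does not reconcile it with the withdrawal and analysis rules in 6.6. If it were enforced, randomised pairs could be lost for a reason related to arm or outcome.

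The size and direction of any bias are unknown. In the assumed scenarios above, the 24-month difference moves from 32 points to between about 29 and 34, and the loss of power is at most about 5 points (81.2% to 76.2%). These figures rest on assumed joining rates of up to about 10% and an assumed doubling of hazard, neither of which comes from the documents. They do not show that the primary comparison is broken. The case for changing the text is that the risk is avoidable and the correction costs almost nothing.

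**What to change.** 1. In 4.3, limit the criterion to participation in another intervention study at the time of inclusion.
2. In 6.6, state that a pair in which either member later joins another intervention study stays in follow-up and in the primary analysis, in its randomised arm. Record the participation and its date, as a deviation or as a co-intervention.
3. In 6.6, define the intention-to-treat set as all randomised pairs, each contributing all available follow-up time and measurements.
4. Say whether later participation in another study counts as a deviation for the on-treatment analysis, so that this is fixed before outcomes are known.

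The cost is the removal of a short phrase in 4.3, a few sentences in 6.6 and one recorded item. Sample size, visits and intervention are unchanged. The downside is small: some co-intervention remains in the comparison, in keeping with a design that already leaves participants free to use other support.
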